Sheehan *et al.*, 1993). Irrespective of the number of ECTs received, ECT would be terminated in any of the following situations: (1) Complete remission of symptoms; (2) significant cognitive impairment (as decided clinically) despite reducing the frequency to twice weekly; (3) medical conditions precluding continuation of ECT; (4) on request from the patient. The patients will be free to withdraw from the study at any point in time – the reason for withdrawal would be documented; (5) if patients develop suicidality amounting to HAM-D suicide item >2. A shared decision for discontinuation would be made after discussing with patients and the treating psychiatrist. 

**Sham-ECT**: Anaesthesia and muscle relaxation would be provided as discussed above, without electrical stimulus. ECT administrator would run the ECT stimulator by keeping electrodes in air, 1–4 times on the first ECT and 1–4 times in subsequent ECTs at a gap of 20–40 secs by setting the incremental electrical parameters. Patients in the sham ECT group would be offered an open-labelled true ECT, if symptoms persist at the end of the blinded trial. Open-labelled true ECT would be offered to patients who withdraw consent from the sham ECT arm due to lack of response.

**
*Adherence to intervention.*
** All sessions would be provided at the hospital by the ECT administration team. The project would cover the hospital expenses of patients. They would also be reasonably compensated for their time and other expenses. Thus, the financial burden of participation in the trial would be minimal. Adverse effects would be monitored diligently, and suitable action would be taken to prevent discomfort. The research team would be available for any clarification/concern regarding the study through easily accessible means (like mobile phone, email). All these measures would encourage the adherence to the intervention and study retention.

**
*Concomitant care.*
** Violation with study guidelines like medication change due to unforeseen situations would be noted down and reported. A change in antipsychotic dose by more than 25% from the dose at the initiation of the intervention, change in antipsychotic medication or initiation of other neuromodulatory interventions would be considered as drop-out. All on-going antipsychotic medication and psychosocial interventions concomitant to the study intervention would be allowed.

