### Outcomes

Primary outcome would be measured as the change in scores from baseline to the end of 9
^th^ session or to the point of premature termination of trial. A comparison of change in Scale for the Assessment of Positive Symptom Scale (SAPS) between the two groups would be the primary outcome measure. Response would be defined as ≥ 40% improvement in SAPS scores (
Petrides *et al.*, 2015), which is similar to the criteria employed in previous ECT studies in schizophrenia (
Ithal *et al.*, 2021).

Secondary outcome measures include other relevant clinical symptoms, adverse effects and neurobiological parameters (the detailed protocol of neurobiological parameters will be described in a separate paper). Time to response would be compared between the two groups. Clinical symptoms would be measured by SAPS, Scale for the Assessment of Negative Symptoms (SANS) (
Andreasen, 1982), BPRS (
Overall & Gorham, 1962) and Auditory Hallucination Rating Scale (AHRS) (
Hoffman *et al.*, 2005) at baseline and every week till the end of the intervention. S-CGI-21 after each ECT (true or sham ECT) session. Functional abilities will be assessed using Groningen Social Disability Schedule (GSDS)(
Wiersma *et al.*, 1988) and social and occupational functioning scale (SOFAS) (
Morosini *et al.*, 2000) at baseline and after each step of intervention. All clinical symptom assessments after baseline will be done 24 hours after the respective ECT session.

Side-effects would be monitored using an ECT-side effect checklist after every ECT. Cognition would be monitored using a weekly Battery for ECT-Related Cognitive Deficits (B4ECT-ReCoDe) (
Viswanath *et al.*, 2013) and Montreal Cognitive assessment (MoCA) from baseline till the end of the trial. Brief Assessment of Cognition in Schizophrenia (BACS) (
Keefe *et al.*, 2004) would be done at baseline and end of the trial. Neurobiological assessments would be performed at baseline and after the end of RCT.

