**Figure 1. f1:**
[figure not shown]
Depiction of study procedure. In the first step of the study, the patients with clozapine resistant or intolerant schizophrenia prescribed electroconvulsive therapy by the clinicians would be randomized to receive 4–6 weeks of True-ECT or Sham-ECT. Patients without clinical response by the end of the intervention in the sham-ECT group would be offered open-label true-ECT in the second step of the study. Neuroimaging, neurophysiological tests would be done at the baseline and end of each step. Blood samples would be collected for genetic polymorphism assays at the baseline. SZ: Schizophrenia, ECT: Electroconvulsive therapy, MRI: Magnetic resonance imaging, EEG: Electroencephalogram, TMS/tDCS: transcranial magnetic stimulation/transcranial direct current stimulation, BDNF: Brain derived neurotrophic factor, COMT: catechol-O-methyltransferase.

**Step-2:** Non-responders (<40% change in SAPS scores in step-1) of sham ECT group or patients who opted for premature termination of trial due to lack of response to the intervention in the step-1 will be given the option to receive true ECT, at the same frequency and similar duration as described in the step-1 of the trial. Written informed consent will be obtained separately prior to the initiation of both steps (
[name] *et al.*, 2022). All the clinical and neurobiological assessments would be repeated in the same frequency as in the step-1 of the study. 

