**Figure 2. f2:**
[figure not shown]
Gantt chart of the assessment timeline in patients. Grey boxes are scheduled timepoints of respective assessments. ECT
_n_= n
^th^ ECT session. *Weekly assessments during the course of treatment will be done every week even if frequency of ECT is reduced to 2/week.

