### Data analysis

Anonymized coded data would be used for analysis. The primary outcome would be assessed as the change in SAPS scores from baseline to post-9th session of treatment using a two-sample t-test. The last observation carried forward method would be used to handle the missing data of those participants who had premature termination of the intervention. The percentage of responders between the two groups would be compared using logistic regression with estimates of adjusted odds-ratio (adjusting for variables including age, sex, duration of illness, antipsychotic daily dose, and anticonvulsant medications). Further, comparison of change in the symptoms scores between the two groups at the end of the interventions would be performed through linear mixed-effects model analysis. The time to response would be compared between the two groups using survival curves. Suitable imputation methods would be used for any missing data at specified time-points. Secondary outcome measures including other psychopathology rating scales, adverse effects and dropout rates would also be compared between the two groups.

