Zervas *et al.*, 2012). Therefore, the administration of nine sham sessions followed by an open-label treatment up to nine sessions as part of the current trial would be well within the current practice of ECT in resistant schizophrenia. In addition, we plan to conduct an interim analysis of the data after 20 participants have been randomized. If we observe that there is a clear disadvantage for sham-ECT participants, then this would be brought to the notice of the IECs and DSMB, and a decision to continue the trial would be revised to avoid exposure of more participants to a less effective treatment. Participants have the right to withdraw from the trial at any point in time. Thus, those who are not satisfied with the level of improvement are free to drop out of the study. We hope that this would address the concerns regarding participants in the sham-ECT limb experiencing less efficacious treatment.

One of the major limitations of the study would be exclusion of severely ill patients who may be having high suicidality or other psychiatric emergency conditions where ECT is known to benefit and those who would lack the capacity to consent to participate in the research. This could be a major subset of patients who receive ECT in clinical settings and this limits the generalisability of the study. The study would be provided as an add-on to the ongoing pharmacotherapy and psychosocial interventions. However, these treatment schedules and doses would be kept stable and would replicate the general clinical care setting where ECT is provided for this group of patients.

We hope that the result of this trial will be able to provide a definitive answer on the efficacy of ECT in clozapine-resistant schizophrenia. This study would provide clues to predictive neurobiological and clinical markers. Therefore, it would enable clinicians to take evidence-based decisions in managing such patients.

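### The primary analysis carries last observations forward although withdrawal is likely to depend on response and may differ by arm, so the estimate can be biased in either direction

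*Protocol article*

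**What the plan says.** The Data analysis section defines the primary comparison as "change in SAPS scores from baseline to post-9th session of treatment using a two-sample t-test" and then fixes the missing-data rule: "The last observation carried forward method would be used to handle the missing data of those participants who had premature termination of the intervention". The Outcomes section builds the same idea into the endpoint, which runs to the ninth session "or to the point of premature termination of trial". A linear mixed-effects model follows as a further comparison, and unspecified imputation is mentioned for missing time points. Neither replaces last observation carried forward (LOCF) for the primary test.

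On leaving early, the Intervention section states: "Open-labelled true ECT would be offered to patients who withdraw consent from the sham ECT arm due to lack of response". Step 2 of the participant timeline repeats the option for "patients who opted for premature termination of trial due to lack of response to the intervention in the step-1". The Discussion adds that "those who are not satisfied with the level of improvement are free to drop out of the study". Under Emergency unblinding, participants learn their arm when their trial participation ends, including when it ends early. The Intervention section also ends treatment at any session for complete remission, persisting cognitive impairment, medical reasons, suicidality or patient request, and the Ancillary care section drops patients whose symptoms worsen.

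SAPS is rated weekly, and the Figure 2 legend confirms this for slower schedules: "Weekly assessments during the course of treatment will be done every week even if frequency of ECT is reduced to 2/week".

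**The concern.** LOCF treats a patient who stops after week 1 as if the week-1 score would still hold at session nine. That is hard to defend when stopping depends on how the patient is doing, and the protocol creates several such links. Sham patients who are not responding can leave and are then offered true ECT. True-ECT patients may be stopped for cognitive effects while still improving. Remitters are frozen at their best score.

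The t-test then compares scores taken after different lengths of treatment, and the mix of lengths can differ by arm. The carried values also enter the test as if observed at session nine, so the standard error makes no allowance for those scores being unknown. At stake is the primary efficacy estimate of a trial that hopes to give a definitive answer.

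**Working it through.** **Planning figure.** The Sample size section gives 45 per group for 80% power at 0.6 SD and alpha 0.05, raised to 50 for dropout. This reproduces: the normal approximation gives 44 per group; the exact two-sided t-test has power 0.795 at 44, 0.804 at 45 and 0.844 at 50. The implied dropout allowance is 1 - 45/50 = 10%, with no split by arm. (Two-sided testing is assumed; the section does not state it.)

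**Inputs from the protocol.** Nine thrice-weekly sessions take 9/3 = 3 weeks, so there are about three weekly SAPS ratings after baseline. The planning effect is 0.6 SD.

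**Inputs assumed.** Dropout shares, time of leaving, and linear improvement over the three weeks. The protocol gives none of these.

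**Bias when leaving is unrelated to response.** Let p be the share of leavers and r the improvement still to come after the last rating, in SD, for sham (S) and ECT (E):

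bias towards ECT = pS × rS - pE × rE

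For leavers after week 1 of 3, r is two thirds of the arm's total improvement. With a true difference of 0.6 SD, ECT improves by the sham amount plus 0.6.

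| Sham change by session nine | rS | rE | Leavers, sham / ECT | Bias (SD) |
|---|---|---|---|---|
| improves 0.8 | 0.533 | 0.933 | 30% / 0% | +0.160 |
| improves 0.8 | 0.533 | 0.933 | 30% / 10% | +0.067 |
| improves 0.4 | 0.267 | 0.667 | 30% / 0% | +0.080 |
| improves 0.4 | 0.267 | 0.667 | 30% / 10% | +0.013 |
| improves 0.4 | 0.267 | 0.667 | 20% / 10% | -0.013 |
| improves 0.4 | 0.267 | 0.667 | 10% / 10% | -0.040 |
| flat | 0 | 0.400 | 30% / 0% | 0.000 |
| flat | 0 | 0.400 | 30% / 10% | -0.040 |
| worsens 0.2 | -0.133 | 0.267 | 30% / 10% | -0.067 |

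If sham improved by a full 1 SD, 30% / 0% would give 0.30 × 0.667 = +0.20.

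**Bias when patients leave for lack of response** (simulated, 50 per arm, true difference 0.6 SD):
- Same withdrawal rule in both arms: bias -0.002 to -0.074 SD.
- With a further 5% per-visit side-effect dropout on ECT: -0.058 to -0.102 SD. At the extreme (sham flat, about 33% leaving each arm) the estimate falls from 0.599 to 0.497 and power from 0.844 to 0.758. The largest power loss in this set is 0.838 to 0.695 (sham improving 0.8 SD, about 23% ECT and 22% sham leavers).

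**False positives when ECT has no effect.**
- Same withdrawal rule in both arms: bias about 0, type I error 0.042 to 0.050.
- Sham-only dropout unrelated to response: 0.057 (20% leaving, sham improves 0.4 SD), 0.069 (30%, 0.4), 0.080 (20%, 0.8) and 0.122 (30%, 0.8).
- Both arms improving 0.6 SD, lag-1 correlation 0.8, poor improvers leaving, 33% sham and 8% ECT: bias 0.10 SD towards ECT and 8.9% false positives, against 5.1% with complete data. An estimator using the weekly scores had bias below 0.01 SD, but missing at random held there by construction.
- At the protocol's own 10% overall, split 15% / 5%, with 0.4 SD still to come: (0.15 - 0.05) × 0.4 = 0.04 SD. With standard error √(2/50) = 0.2 SD the shift is 0.04/0.2 = 0.2 standard errors, and rejection is about 5.5%.

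**The case against.** A reader might infer that the offer of true ECT to sham leavers builds a bias towards ECT into the primary estimate. The documents do not support that. Patients, caregivers and treating psychiatrists are masked, and the arm is disclosed only once participation has ended, so patients decide to leave without knowing their arm. If ECT has no effect and masking holds, one withdrawal rule gives equal dropout, and the false-positive rate stays nominal. The 8.9% figure needs about a four-fold dropout imbalance under no effect. LOCF also cuts short true-ECT patients who stop for cognitive or medical reasons, which works against ECT. The roughly 20% sham improvement in the Background comes from one earlier study, with no time course, and does not show that non-improving leavers would have gone on to improve. All of this stands. It removes the fixed direction, and the 10% dropout allowance argues for a smaller bias than the extreme scenarios.

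It does not rescue the rule. With a real effect on SAPS, lack-of-response dropout differs by arm even under perfect masking. The Masking section itself regards the risk of unblinding as high when immediate adverse effects are assessed, and patients experience those effects themselves.

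It can also be said that LOCF matches the endpoint wording in Outcomes, that a mixed model is planned anyway, and that sensitivity analyses may be in an analysis plan not shown. The absence of sensitivity analyses is accordingly not criticised. The point is what the protocol does fix: LOCF as the primary rule, with the better-suited model placed second. Nor do the endpoint wordings fully agree, since Data analysis names only the post-session-nine change.

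**Conclusion.** The concern holds without a fixed direction. LOCF is the primary missing-data rule in a design where withdrawal is likely to be informative and may be unequal between arms. The primary estimate can then be biased and its uncertainty understated. The bias is towards ECT if sham patients leave more often and would have kept improving. It is against ECT, with loss of power, if improving ECT patients stop early. Some scenarios give none.

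Over the scenarios examined the bias is roughly -0.10 to +0.16 SD, that is, up to 0.16/0.6 = 27% of the planning effect one way and 0.10/0.6 = 17% the other. Every figure rests on assumed dropout shares and trajectories; the 8.9% false-positive rate is one such scenario, not a property of the design. This should be fixed, but it does not invalidate the trial.

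**What to change.** 1. Make the planned mixed model primary, using all blinded-phase SAPS ratings with arm-by-visit terms, baseline SAPS and centre, and take the ECT minus sham contrast at the post-session-nine assessment.
2. State how patients moved to twice-weekly sessions map to that assessment. Nine sessions take 3 weeks at three per week but 9/2 = 4.5 weeks at two per week, so a plain week-3 contrast would not be session nine for them.
3. Exclude SAPS ratings taken after open-label ECT starts.
4. Align the endpoint wording in Outcomes with that in Data analysis.
5. Keep the LOCF t-test as a sensitivity analysis. Add a delta-adjusted analysis that varies the assumed course of leavers in both arms, optionally with reference-based imputation. Sham-based imputation alone is not enough, because for sham leavers it amounts to missing at random and leaves that assumption untested.

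The cost is a change of wording and a little more programming. No new data are needed, since SAPS is already collected weekly, and 50 per group stands. The downside is reliance on missing at random in the primary model, which the delta-adjusted analysis is there to probe.

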### Data monitoring

**
*Formal committees.*
** The DSMB, an independent advisory body, would evaluate the data during the course of the study contributing to the scientific and ethical integrity of the study. It would periodically review and evaluate clinical efficacy and safety data collected during the study, and assess reports on cumulated SAE. It consists of a biostatistician, psychiatrist, and ethicist with a specialization in psychiatry. The board, based on the DSMB charter, will provide a report of recommendation on the continuation, modification, suspension, or termination of the trial to the study sponsor. The sponsor will submit the report to the ethics committees and the TMG to decide the next course of action.

The TMG will comprise a group of investigators from the three collaborating institutes. It will monitor the day-to-day execution of the trial. It would take cognizance of trial participant drop-out in the event of withdrawal of consent, noncompliance with study guidelines, and worsening of symptoms. It would interact with the DSMB and Institute Ethics Committee (IEC). It would review the reports and recommendations of these oversight/monitoring committees and plan appropriate actions. It would decide on trial terminations and any trial modifications of the study procedures. It would also oversee the submission of modification, premature termination (if any), and final (completed) trial summary report to the IEC, trial registries, and funding agency.

The data management committee comprises the principal investigators of the three institutes. It would be dedicated to reviewing the data archival, management, and sharing. It would execute the periodic data auditing and audit of the research practices related to the studies. It would ensure anonymization and de-identification of data. It would monitor the storage of data in the encrypted data storage servers. It would oversee the sharing of de-identified data upon reasonable requests from collaborators or the research community. Public access would be granted as per the policy of DBT-Wellcome trust India Alliance and international good research practices in strict compliance with the ethics guidelines for biomedical research in India.

### Interim analysis

We plan to conduct an interim analysis of the data after 20 patients in each group have been randomized. This will be shared with the DSMB and if it observes that there is a clear disadvantage to the sham-ECT patients then this would be brought to the notice of the ethics committee. A decision to continue the trial would be revised to avoid exposure of more patients to a less effective treatment by TMG. If a clear level of adversity from ECT proves to be above a predefined threshold that is clinically significant as deemed by DSMB and TMG, the trial would be discontinued to prevent any undue harm to patients in consultation with the ethics committee.

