## Methods

### Trial design

We employ a parallel-arm double-blind randomized sham-controlled design with an allocation ratio of 1:1 to determine the differential efficacy of add-on electroconvulsive therapy to sham-electroconvulsive therapy in clozapine-resistant/intolerant schizophrenia.

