### Sample size

A total of 100 patients would be recruited for the study. A meta-analysis has found an effect size of 0.88 for clozapine with ECT as compared to clozapine alone (
Wang *et al.*, 2018). The sample size for this study was calculated using a more conservative estimate of effect size 0.6 for a sham-controlled trial, to account for potential placebo response in the sham group. Given an effect size of 0.6 between the treatment groups for change in positive symptom severity, a minimum sample of 45 in each group would have 80% power to detect post-treatment differences between the two groups with an alpha of 0.05 in a two independent sample t-test. In order to account for dropouts, we propose to recruit 50 patients in each group. For comparison studies between patients and healthy controls, a sample size of at least 100 healthy subjects would offer optimal power as per the sample size of previous neurobiological studies in this area (
Goyal *et al.*, 2011;
Mouchlianitis *et al.*, 2016;
Raymond *et al.*, 2022).

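### The interim can end the trial because sham ECT is less effective, on an undefined criterion, while the final t-test keeps the full 0.05: type I error is not controlled as written

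*Protocol article*

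**What the plan says.** All references are to the protocol article.

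- **Interim analysis (Methods).** A look at the data is planned once 20 patients in each group have been randomised. The results go to the DSMB. If sham patients are at a clear disadvantage, the ethics committee is told and "A decision to continue the trial would be revised to avoid exposure of more patients to a less effective treatment by TMG". The rule for harm from ECT, in the same section, refers to a predefined threshold. The rule for sham being less effective refers to none.
- **Sample size.** The assumed standardised difference in positive-symptom change is 0.6. On that basis, "a minimum sample of 45 in each group would have 80% power". The test behind this figure is described as one "with an alpha of 0.05 in a two independent sample t-test". Recruitment is then raised to 50 per arm to allow for dropouts. No alpha is set aside for an interim look.
- **Data analysis.** The primary comparison is a two-sample t-test of SAPS change to the ninth session, with no adjustment for an earlier look.
- **Data monitoring.** Of the DSMB: "It would periodically review and evaluate clinical efficacy and safety data collected during the study". The board works from a charter that is not shown. Decisions to terminate the trial lie with the trial management group (TMG), which is made up of investigators.
- **Discussion.** The same interim is placed after 20 participants have been randomised. The authors observe any sham disadvantage and then bring it to the ethics committees and the DSMB.
- **Allocation (Masking).** Investigators and data analysts are blinded to study arm.

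**The concern.** Ending the trial to spare patients a less effective treatment means ending it because ECT appears superior. That gives the trial two chances to produce a positive result, while the stated error rate allows for one. Without a numerical criterion, the false-positive rate of the primary claim depends on a judgement made after arm-level data have been seen.

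An efficacy stop on few patients also selects large observed differences, so the reported effect would tend to be too big. This matters here because the authors present the trial as the way to settle whether ECT works in this population, and they hope for a definitive answer.

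The conflicts between sections add to the problem. As written, a reader cannot tell how much data the look uses, or whether blinded investigators see results by arm before the independent board does.

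**Working it through.** **1. The plan's own figure.** Inputs from Sample size and Trial design: d = 0.6, alpha 0.05, power 80%, "allocation ratio of 1:1". The two-sample t-test (noncentral t, two-sided) needs 44.6, so 45 per arm, and power at 45 is 0.804. The stated 45 reproduces. A one-sided 0.05 would need only about 35, so the figure corresponds to two-sided 0.05 spent entirely on one final test. Dividing 45 by 0.90 gives 50; the 10% dropout is an assumption, since the article states none.

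**2. Overall error with one interim look.** Let Z1 and Z2 be the interim and final test statistics. Under no effect they are bivariate normal with correlation √f, where f is the information fraction. With 20 per arm, f = 40/100 = 0.40; against the 90 analysable patients, f = 40/90 = 0.44. The rule looks in one direction only (sham worse), so

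overall error = P(Z1 > c1 or |Z2| > 1.96).

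The article gives no c1, so the interim p-values below are assumptions.

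| Assumed meaning of clear (two-sided p) | f = 0.40, sham-worse stops only | f = 0.40, both directions | f = 0.20 (20 in total), sham-worse only |
|---|---|---|---|
| p<0.05 | 6.8% | 8.6% | 7.1% |
| p<0.01 | 5.3% | 5.6% | 5.4% |
| p<0.001 | 5.02% | 5.04% | 5.03% |

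At f = 0.44 the p<0.05 figure is 6.7% (8.5% in both directions). A simulation of actual t-tests, 400,000 trials per setting, gave 6.7% and 8.5% for 20 of 50 per arm at p<0.05.

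**3. Exaggeration of the effect.** With 20 per arm (38 degrees of freedom) the critical t at two-sided 0.05 is 2.024. Stopping therefore needs an observed d of at least 2.024 × √(2/20) = 0.64, which is above the planned 0.6. If the true d were 0.3 (an assumption), about 15% of trials would stop, and the mean observed d among them would be about 0.82.

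**4. With a boundary.** Hold the overall two-sided error at 5% with f = 0.40:

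- Interim p<0.001 (Haybittle-Peto): final level 0.0496.
- Lan-DeMets O'Brien-Fleming: interim p about 0.0008, final level 0.0497.
- Pocock: about 0.028 at each look.

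Power at 45 per arm and d = 0.6 is 0.803 at a final level of 0.0497. At a final level of 0.03 it would be 0.738, so a Pocock boundary would be costly. The chance of crossing p<0.001 at 20 per arm if d = 0.6 is 6.4%.

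**5. Sections side by side.** Interim analysis: 40 patients, DSMB informed. Discussion: 20 patients, authors observe first and then inform the DSMB. Masking: investigators and analysts blinded. Seeing that sham is worse requires identified arms, so these statements cannot all hold without further explanation. Both sections also count patients randomised, so fewer than that number may have the ninth-session outcome at the look.

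**The case against.** The strongest objection is that this is a condensed article. The board has a charter and includes a biostatistician, and boundaries are often set in a charter or an analysis plan. No sentence says that the interim will be tested at 0.05. The alpha of 0.05 is a sample-size input, and a strict boundary would leave it almost unchanged. The stop is not automatic either: it passes through the ethics committee and the TMG. If a stop were never claimed as a positive result, it would not inflate the error.

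Much of this stands, and it limits the size of the point. It does not remove it. The article itself fixes an efficacy-driven consequence, an undefined criterion and an unadjusted final test. It cites a predefined threshold for harm and none for efficacy. It also contradicts itself on the timing and handling of the look.

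Three stronger readings are tempting, and the article does not support them:

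- **The false-positive rate definitely exceeds 5% by a material amount.** That depends on what clear means; at p<0.001 the excess is negligible.
- **The error is 8.6%.** That figure counts interim stops in both directions, whereas the rule concerns sham being worse.
- **There will be several efficacy tests, with a correspondingly larger error.** Periodic review of efficacy data is common wording for a board. The article names one interim analysis and gives no schedule of repeated tests.

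**Conclusion.** The point holds in this form: type I error for the primary comparison is not controlled as written. For a look at 20 per arm and a final two-sided 0.05, the overall error runs from about 5.0% (p<0.001) through 5.3% (p<0.01) to 6.8% (p<0.05). If the look is at 20 patients in total, the last figure is 7.1%.

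The range rests on three assumptions: the listed p-values stand in for the undefined criterion, an early stop would be reported as evidence for ECT, and the unseen charter holds no boundary. The exaggerated estimate at an early stop (about 0.82 when the true d is 0.3) applies to the p<0.05 reading.

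The conflict over interim size and first viewer needs none of these assumptions. The sample-size figure itself is correct for a single look.

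**What to change.** 1. In Interim analysis, consistent with the DSMB charter, declare one efficacy look and give a numerical boundary on the primary comparison. Examples are two-sided p<0.001, or a Lan-DeMets O'Brien-Fleming boundary (about 0.0008 at 40% information).
2. State the final level, about 0.0496 to 0.05. Keeping exactly 0.05 after a p<0.001 look gives at most 5.04%.
3. State that the DSMB's other periodic reviews carry no efficacy stop.
4. Reconcile Interim analysis, Discussion and Masking on when the look occurs and on who sees results by arm.

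The cost is a few sentences in the protocol and charter, made before the interim takes place. The sample size stays the same and power at 45 per arm remains about 80%. The downside is that an early efficacy stop becomes unlikely, with about a 6% chance if the true d is 0.6.
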